### Brief Eligibility Interview

|         |                            |                                                     |
|---------|----------------------------|-----------------------------------------------------|
| Center: | Study Staff Name:
_____ | Today's Date:
____/____/20____
Day Month Year |
|---------|----------------------------|-----------------------------------------------------|

**Must all be YES to participate?**

- Requests circumcision and would potentially like to be part of a study? Yes ☐ No ☐
- At least 18 years of age? Yes ☐ No ☐
- Able to provide informed consent to participate? Yes ☐ No ☐
- Willing to participate in 2 follow-up visits? Yes ☐ No ☐
- Generally healthy? Yes ☐ No ☐

**Must all be NO to participate?**

- Any current significant illness? Yes ☐ No ☐
- Experiencing urethral discharge? Yes ☐ No ☐
- Currently taking aspirin? Yes ☐ No ☐
- Past reaction to local anesthetic? Yes ☐ No ☐
- Known bleeding disorder or tends to bleed profusely when cut? Yes ☐ No ☐

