**SUMMARY**

According to the Framework for Clinical Evaluation of Devices for Adult Male Circumcision (WHO, 2011): *“WHO and other health authorities wish to identify one or more devices that (a) would make the VMMC safer, easier, and quicker; (b) would have more rapid healing than current methods and/or might entail less risk of HIV transmission in the post-operative period; (c) could be performed safely by health-care providers with a minimal level of training; and (d) would be cost-effective compared to standard surgical methods for male circumcision scale up.”*

Because of difficulties and small risks entailed in using sterilizable instruments, WHO prefers disposable, single-use-only instruments be used for circumcision. This proposed randomized controlled trial will provide important data which will inform and enable the South African health system to more effectively scale-up circumcision services. This study will prove that VMMC using the Unicirc disposable single-use-only instrument coupled with tissue adhesive meets WHO criteria for the ideal method: it is faster, easier to learn, safer for both surgeons and patients, heals sooner, has excellent cosmetic results, and is more cost effective than any other currently available technique.

We propose a randomized controlled trial (RCT) comparing this minimally-invasive circumcision technique to the open surgical technique. In accordance with WHO recommendations concerning sample size found in the Framework for Clinical Evaluation of Devices for Adult Male Circumcision, we propose to study:

- Unicirc disposable instrument with topical anaesthetic and tissue adhesive wound sealing: 50 men
- Open surgical circumcision: 25 men

This is the fourth study of Unicirc circumcision, and the second study that uses topical anaesthetic instead of injectable local anaesthetic. Tissue adhesive is widely used in multiple areas of medicine; specifically, multiple observational studies and RCTs have shown cyanoacrylate tissue adhesives to be superior to suture closure in VMMC. The open surgical method will serve as the control intervention.

*Population:* Men at least 18 years of age who desire male circumcision

*Study design:* Randomized controlled trial

*Intervention:* Unicirc instrument circumcision plus tissue adhesive vs. open surgical circumcision

*Follow-up visits:* 7 days and 28 days. Optional 42 day follow-up if not completely healed by 4 weeks.

*Primary outcome:* Intraoperative time

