**Volunteer is potentially eligible to participate**

Yes ☐ No ☐

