| Center: | Participant Number:

 | Study Staff Name:

 | Today's Date:

 

 
 
 Day Month Year 
 |
|----------------|-------------------------------------------------------------------------------------------------------------------|-----------------------------------------------------------------------------------------------------------------|-------------------------------------------------------------------------------------------------------------------------------------------------------------------------------------------------------------------------------------------------------------------------------------------------------------------------------------------------------------------------------------------------------------------------------------------------------------------------------------------------------------------------------------------------------------------------------------------------------------------------------------------------------------------------------------------------------------------------------------------------------------------------------------------------|

- 1) Eligibility Interview Inclusion/Exclusion ☐ COMPLETE
  - a. ☐ Excluded
  - b. ☐ Included -----> Start Informed Consent Process
  
- 2) Participant agrees to return for control at 7 days and 4 weeks. ☐ COMPLETE
  
- 3) Informed Consent ☐ COMPLETE
  - a. Not signed -----> Excluded
  - b. Signed -----> Continue
    - Respond to all of participant's questions.
    - Give the participant a copy of the informed consent
  
- 4) Assign the participant number and sign the form ☐ COMPLETE.
  
- 5) Fill in the participant's contact info ☐ COMPLETE
  
- 6) Initial questionnaire ☐ COMPLETE
  - a. Complete the questionnaire with the participant -----> Conduct Physical Exam
  
- 7) Physical Exam
  - a. General exam ☐ COMPLETE AND NO EXCLUSIONS
    - i. Genital Exam ☐ COMPLETE AND NO EXCLUSIONS
  
  - b. Schedule circumcision. ☐ COMPLETE

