|---------|--------------------------------------------------|--------------------------|----------------------------------------------------------------------------------------------------------------------------------------------------------------------------------------------------------------------------------------------|
| Center: | Participant Number:                              | Study Staff Name:        | Today's Date:                                                                                                                                                                                                                                |
|         | 
 

 

 

 
 | 
 

 
 | 
 
 

 

 
 
 

 

 
 
 
2
 
0
 
1
 
 
 

 

 
 
 
 
Day
 
Month
 
Year
 
 |

1. Blood pressure (mm Hg):   |\_|\_|\_|\_|/|\_|\_|\_|\_|

2. Weight in kilograms (kg):       |\_|\_|\_|\_|.

3. Does the participant have any of the following conditions or complaints? (Mark ☒ )

**4. Does the participant have any medication allergies?...|\_\_\_\_| (Include all anesthetic and other drug, and latex allergies)**  
 0 = No → **GO TO QUESTION 6**  
 1 = Yes

- | Allergy:  | Reaction: |
|-----------|-----------|
| 5a. _____ | _____     |
| 5b. _____ | _____     |
| 5c. _____ | _____     |
| 5d. _____ | _____     |

- 12a. If YES, describe:**

14a. If NO, specify:

- If 0 = NO, COMPLETE SCREENING CHECKLIST  
and FINAL STATUS CRFs.**

Date (DD/MM/YYYY):

Unicirc 004

|         |                        |                      |                                             |
|---------|------------------------|----------------------|---------------------------------------------|
| Center: | Participant
Number: | Study Staff
Name: | Date of Visit:                              |
|         | _ _ _                  | _ _ _                | _ _ _ / _ _ _ /2 0 1 _ _ 
Day Month Year |

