**The Participant has:**

**Yes No**

- ☐ ☐ Allergy to local anaesthetic
- ☐ ☐ Hemophilia or easy bleeding
- ☐ ☐ Anemia
- ☐ ☐ Currently taking aspirin?

- ☐ ☐ Urethral Discharge
- ☐ ☐ Genital ulcers or warts
- ☐ ☐ Difficulty with sexual function or erections
- ☐ ☐ Painful or difficult urination
- ☐ ☐ Other problem \_\_\_\_\_

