### Post-Operative Instructions Unicirc

Participant ID \_\_\_\_\_

If you have complications or questions, call the Doctor.

Doctor's name and phone contact \_\_\_\_\_

Phone number of Medical Centre \_\_\_\_\_

- Swelling is normal in the first week, but if the wound hurts or swells more or gets redder, call the doctor.

- Take paracetamol, two tablets every 4-6 hours when needed for pain (up to 8 tablets per 24 hours)

The adhesive tape (Hypafix) should remain in place for 7 to 10 days, until it falls off. If it has not fallen off by 2 weeks, wet the area and remove it gently.

How to care for your wound:

- Leave only the tape as a dressing. The tape should stay dry.

- You may wash briefly but do not soak or scrub the area. To dry, rub gently with a soft towel.

- Avoid ointments. Do not apply creams or lotions, creams, Vaseline or any other product to the wound.

- Do not rub, scratch or pick at the wound.

- Redness, swelling and pain are common at first, and should be less every day. Contact us if there is increased redness, swelling or pain, if the wound is hot to the touch, or if the wound edges reopen or separate.

| Follow-up visits   | Date |
|--------------------|------|
| 7 days             |      |
| 4 weeks            |      |
| 6 weeks (optional) |      |

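### No visible screening item asks about past reactions to the tissue adhesive or adhesive tape planned for the Unicirc arm

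*Protocol*

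**What the plan says.** **Materials used.** The protocol SUMMARY describes the experimental arm as "Unicirc disposable instrument with topical anaesthetic and tissue adhesive wound sealing: 50 men"; the comparator is open surgery in 25 men. On the Surgical Report Form, under The surgical procedure, tissue adhesive appears on the Unicirc line and not on the open surgery line. The sheet headed Post-Operative Instructions Unicirc adds: "The adhesive tape (Hypafix) should remain in place for 7 to 10 days". It also says what to do if the tape is still on at two weeks.

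**Screening.** Three legible places deal with allergy or past reactions:

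- The list headed Must all be NO to participate? has five items. The only one about a reaction to a product is "Past reaction to local anesthetic".
- Question 4 of the screening medical form (headed Unicirc 004) asks about medication allergies, with the scope note "Include all anesthetic and other drug, and latex allergies". A No sends the interviewer to question 6, past the open lines 5a to 5d for allergen and reaction.
- The Surgical Report Form, in the list of what the participant has, gives "Allergy to local anaesthetic" and ends with a free line for any other problem.

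**The concern.** In a two-arm randomised trial every man allocated should be a suitable candidate for either arm. The screen should therefore cover the materials specific to each technique. Here it covers the anaesthetic three times and latex once, but no visible item covers the two materials used to close and cover the wound in the experimental arm. The mention of latex shows that the authors regard an allergy to a contact material as relevant, so the omission does not look deliberate.

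At stake is participant safety. A man who knows that he reacts to skin glue or plaster could have one or both applied to a fresh genital wound because nobody asked him.

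**Working it through.** The plan gives no figure on this point, so there is none to reproduce. The check sets each screening step against the materials used.

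| Step in the protocol | What it covers | Prompts for adhesive or tape? |
|---|---|---|
| Brief Eligibility Interview, exclusion list | Current illness, urethral discharge, aspirin, reaction to local anaesthetic, bleeding tendency | No |
| Screening medical form, question 4 | Anaesthetics, other drugs, latex | No |
| Screening medical form, lines 5a to 5d | Open, but skipped after a No to question 4 | No |
| Flowsheet, general and genital examination | Physical findings | No |
| Surgical Report Form, participant list | Local anaesthetic, plus a free line | No |

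**Path of a man with a known adhesive reaction and no other allergy.**

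1. He answers No to all five exclusion items and is recorded under "Volunteer is potentially eligible to participate".
2. At question 4 he can truthfully answer No, because plaster and skin glue are neither drugs nor latex. The open lines are then skipped.
3. The flowsheet examination can be marked "COMPLETE AND NO EXCLUSIONS", since an examination does not reveal a history of contact reaction.
4. On the Surgical Report Form he has no allergy to local anaesthetic. He might mention plaster under the free line, but nothing prompts him, and nothing visible makes an entry there an exclusion.

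**Planned exposure.** 50 / (50 + 25) = 50/75, or two thirds of the men randomised.

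**Frequency.** The documents give no rate of past reactions. Purely as an assumption, let 0.5% to 3% of men report one, and let the screen detect none of them:

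- Expected number among the 50: 50 × 0.005 = 0.25, up to 50 × 0.03 = 1.5.
- Chance of at least one among the 50: 1 − 0.995^50 = 22%, up to 1 − 0.97^50 = 78%.

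These figures describe enrolling a man with such a history, not a complication occurring.

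**The case against.** **The visible forms are incomplete.** This is the strongest point against. On the screening medical form the list of conditions under question 3 and most items from question 6 to question 14 are not legible. The form ends in a stop instruction, "If 0 = NO, COMPLETE SCREENING CHECKLIST", whose question is lost, and the checklist it refers to is not shown. Part of the Surgical Report Form is also missing. An adhesive item could sit in any of these places. This stands, and it limits the point to visible items. It does not reach the exclusion list, which appears complete, or the scope note of question 4, which is legible.

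**The interview is only a preliminary filter.** True, but the later steps do not close the gap, as the path above shows.

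**Stronger readings that the documents do not support.**

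- A reader might infer that adhesive reactions would contaminate the safety comparison. They would not: the tested intervention includes the adhesive, so a reaction to it is a genuine harm of that package. Nor need it be recorded as infection or dehiscence, since the follow-up forms have an item for other complications and the adverse event form asks for a description.
- A reader might infer dropout or crossover in one arm when an allergy is noticed at surgery. The visible text does not show when allocation takes place relative to the Surgical Report Form checks.
- A reader might take the tape risk as confined to the Unicirc arm. Only the Unicirc aftercare sheet is shown, and the control dressing is not described.
- A reader might take 22% to 78% as a risk of complications. It rests on an assumed prevalence and says nothing about how often a past reaction recurs or how severe it is.

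**Conclusion.** The point holds for the visible screen. No legible item asks about tissue adhesive or adhesive tape, although all 50 Unicirc men are planned to receive the adhesive and their instructions assume the tape. Followed as written, the screen can pass a man with a known adhesive reaction and make him available for allocation to an arm that does not suit him.

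This is an avoidable safety risk in the Unicirc arm; for tape, use in the control arm is unknown. It does not affect intraoperative time, the primary outcome, or any number stated in the protocol. Its frequency cannot be derived from the documents, and the range under working is only illustrative. The conclusion assumes that no illegible or unshown item on the forms already covers adhesive and tape, which the sponsor can confirm by looking at the full forms.

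**What to change.** Check the complete screening forms first. If they do not already cover it, bring the screen into line with the materials used:

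- Add a question on past reaction to tissue adhesive or adhesive tape to the list headed Must all be NO to participate?.
- Name adhesive and tape in the scope note of question 4 on the screening medical form and in the allergy line of the Surgical Report Form.
- Ask it of all men before allocation, so that both arms are drawn from men eligible for either technique.

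The cost is one question added to three existing forms, and a few men may be screened out. Under the same assumed 0.5% to 3%, the expected number among 75 men is 75 × 0.005 = 0.4 to 75 × 0.03 = 2.3, so possibly one or two. No analysis or sample size needs to change.

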**Volunteer is potentially eligible to participate**

Yes ☐ No ☐

## Flowsheet for Potential Participants

### Unicirc 4 Trial

|                |                                                                                                                   |                                                                                                                 |                                                                                                                                                                                                                                                                                                                                                                                                                                                                                                                                                                                                                                                                                                                                                                                                 |
|----------------|-------------------------------------------------------------------------------------------------------------------|-----------------------------------------------------------------------------------------------------------------|-------------------------------------------------------------------------------------------------------------------------------------------------------------------------------------------------------------------------------------------------------------------------------------------------------------------------------------------------------------------------------------------------------------------------------------------------------------------------------------------------------------------------------------------------------------------------------------------------------------------------------------------------------------------------------------------------------------------------------------------------------------------------------------------------|
| Center: | Participant Number:

 | Study Staff Name:

 | Today's Date:

 

 
 
 Day Month Year 
 |
|----------------|-------------------------------------------------------------------------------------------------------------------|-----------------------------------------------------------------------------------------------------------------|-------------------------------------------------------------------------------------------------------------------------------------------------------------------------------------------------------------------------------------------------------------------------------------------------------------------------------------------------------------------------------------------------------------------------------------------------------------------------------------------------------------------------------------------------------------------------------------------------------------------------------------------------------------------------------------------------------------------------------------------------------------------------------------------------|

- 1) Eligibility Interview Inclusion/Exclusion ☐ COMPLETE
  - a. ☐ Excluded
  - b. ☐ Included -----> Start Informed Consent Process
  
- 2) Participant agrees to return for control at 7 days and 4 weeks. ☐ COMPLETE
  
- 3) Informed Consent ☐ COMPLETE
  - a. Not signed -----> Excluded
  - b. Signed -----> Continue
    - Respond to all of participant's questions.
    - Give the participant a copy of the informed consent
  
- 4) Assign the participant number and sign the form ☐ COMPLETE.
  
- 5) Fill in the participant's contact info ☐ COMPLETE
  
- 6) Initial questionnaire ☐ COMPLETE
  - a. Complete the questionnaire with the participant -----> Conduct Physical Exam
  
- 7) Physical Exam
  - a. General exam ☐ COMPLETE AND NO EXCLUSIONS
    - i. Genital Exam ☐ COMPLETE AND NO EXCLUSIONS
  
  - b. Schedule circumcision. ☐ COMPLETE

**Screening Visit: Demographics**  
**Unicirc 004**

|                |                                        |                                      |                                                                      |
|----------------|----------------------------------------|--------------------------------------|----------------------------------------------------------------------|
| Center: | Participant Number:
 _ _ _ _ | Study Staff Name:
 _ _ _ _ | Today's Date:
 _ _ _ / _ _ _ /2 0 1 _ _ 
Day Month Year |
|----------------|----------------------------------------|--------------------------------------|----------------------------------------------------------------------|

1. What is the participant's age?..... |\_|\_|\_|\_|

2. What is the participant's relationship with his primary sex partner (wife or steady girlfriend)?..... |\_|\_|

- 1 = Married and living with wife
- 2 = Married and not living with wife
- 3 = Not married with regular partner
- 4 = No primary sex partner
- 5 = Polygamous
- 6 = Other, specify: \_\_\_\_\_

3. What is the participant's highest level of academic education? ..... |\_|\_|

- 1 = No formal education
- 2 = Some Primary
- 3 = Completed Primary
- 4 = Some Secondary
- 5 = Completed Secondary
- 6 = Post Secondary
- 7 = Other, specify: \_\_\_\_\_

4. What is the participant's religion? |\_|\_|\_|\_|

- 01 = Christian
- 02 = Muslim
- 03 = Nomiya
- 04 = African Independent Church
- 05 = Hindu
- 06 = No religion
- 07 = Other, specify: \_\_\_\_\_

5. What is the participant's primary reason for circumcision?..... |\_|\_|

- 1 = Partial HIV protection
- 2 = Hygiene
- 3 = Social / Religious
- 4 = Appearance
- 5 = Sexual Pleasure
- 6 = Medical, explain: \_\_\_\_\_

7 = Other, specify: \_\_\_\_\_

Initials of person completing form: \_\_\_\_\_

Date (DD/MM/YYYY): \_\_\_\_\_

|         |                                                  |                          |                                                                                                                                                                                                                                              |
|---------|--------------------------------------------------|--------------------------|----------------------------------------------------------------------------------------------------------------------------------------------------------------------------------------------------------------------------------------------|
| Center: | Participant Number:                              | Study Staff Name:        | Today's Date:                                                                                                                                                                                                                                |
|         | 
 

 

 

 
 | 
 

 
 | 
 
 

 

 
 
 

 

 
 
 
2
 
0
 
1
 
 
 

 

 
 
 
 
Day
 
Month
 
Year
 
 |

1. Blood pressure (mm Hg):   |\_|\_|\_|\_|/|\_|\_|\_|\_|

2. Weight in kilograms (kg):       |\_|\_|\_|\_|.

3. Does the participant have any of the following conditions or complaints? (Mark ☒ )

**4. Does the participant have any medication allergies?...|\_\_\_\_| (Include all anesthetic and other drug, and latex allergies)**  
 0 = No → **GO TO QUESTION 6**  
 1 = Yes

- | Allergy:  | Reaction: |
|-----------|-----------|
| 5a. _____ | _____     |
| 5b. _____ | _____     |
| 5c. _____ | _____     |
| 5d. _____ | _____     |

- 12a. If YES, describe:**

14a. If NO, specify:

- If 0 = NO, COMPLETE SCREENING CHECKLIST  
and FINAL STATUS CRFs.**

Date (DD/MM/YYYY):

Unicirc 004

|         |                        |                      |                                             |
|---------|------------------------|----------------------|---------------------------------------------|
| Center: | Participant
Number: | Study Staff
Name: | Date of Visit:                              |
|         | _ _ _                  | _ _ _                | _ _ _ / _ _ _ /2 0 1 _ _ 
Day Month Year |

